### Safety assessment

The information of adverse events (AEs) related to interventions including infection, bloody swelling, stabbing pain, broken needle, hemorrhage, palpitation, syncope, headache will be monitored and recorded in the case report forms (CRF) by a research assistant. Serious AEs will be handled by emergency medicine physicians or acupuncturists. Moreover, serious AEs will be reported to the Ethics Committee of Hospital of Chengdu University of Traditional Chinese medicine.

### Data collection and quality control

The data will be collected alone on CRF by the same evaluator and will be imported into the computer respectively by two research assistants who are not involved in the trial to avoid bias in the results. All personnel involved in the study will be required to complete professional training to ensure the quality of the trial. This training will cover details of the trial, including the introduction of inclusion and exclusion criteria, completion of CRF, acupuncture procedures, and data entry methods.

### Sample size calculation

The primary outcome of this study is the mean difference in NRS scores for BC between the baseline and the endpoint. Sample size calculations will be based on a previous neuroimaging study of acupuncture in BC [41], which reported mean differences in NRS scores of -1.74 ± 1.543 for the acupuncture group and -0.66 ± 0.986 for the sham acupuncture group. Accordingly, a total of 76 patients will be calculated using a 2-sided test with a 5% significance level and 90% power. To account for a 10% dropout rate, this trial will ultimately enroll 86 patients.

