### Randomization and allocation

Baseline evaluation will be conducted for eligible subjects. The random sequence will be generated using SAS® 9.4 software (SAS Institute Inc., North Carolina, USA). The random sequence will be recorded on sealed and opaque envelopes, with the random numbers of the two groups inside. Moreover, these envelopes will be opened sequentially by a researcher assistant who is not involved in the data collection or acupuncture treatment. In addition, the researcher assistant will randomly assign the subjects to the acupuncture group and the sham acupuncture group with ratio of 1:1.

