## Discussion

BC is one of the 64 diseases that are suitable for acupuncture treatment, as recommended by the World Health Organization [42]. The studies of acupuncture treatment for BC have reported that acupuncture has play therapeutic effect on BC [43–46]. However, the quality of evidence supporting the use of acupuncture for BC is limited due to methodological limitations. Furthermore, some studies have shown that sham acupuncture, such as needle insertion into wrong or non-points, or superficial needling at non-points, may produce efficacious results [47, 48]. Therefore, it is necessary to use non-penetrating needling as the control group to produce a smaller, nonspecific effect [49].

Several clinical studies have proposed that acupuncture on GB34 could significantly improve the symptoms of patients with BC [50, 51]. Furthermore, GB34 is located on the lower limbs of the patient, making it difficult for them to observe the treatment procedure and needle site while in a supine position. Therefore, the selection of acupoints is likely to increase the likelihood of patient-blinding.

In this trial, there are several limitations that need to be acknowledged. Firstly, blinding of acupuncturists is not possible due to the unique nature of acupuncture procedures. Secondly, the small sample size may lead to inconclusive results. Finally, there is a potential for a relatively high dropout rate in the sham acupuncture group.

To summarize, this trial aims to investigate the efficacy and safety of acupuncture in relieving pain and pain-related symptoms in patients with BC by controlling the quality of acupuncturist’s operation and implementing assignment blinding. The results of this trial are expected to provide an alternative treatment option for patients with BC and contribute to the development of guideline recommendations.

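### The stated 76 patients do not follow from the stated inputs at 90% power: those inputs give 62 to 64, and 76 gives about 95% power

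*Protocol article*

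**What the plan says.** The Sample size calculation section of the protocol article gives every input of a standard comparison of two means. The planning values come from one previous neuroimaging study: "mean differences in NRS scores of -1.74 ± 1.543 for the acupuncture group and -0.66 ± 0.986 for the sham acupuncture group". The error rates are set by "using a 2-sided test with a 5% significance level and 90% power". The section presents 76 as the consequence of these inputs: "Accordingly, a total of 76 patients will be calculated using a 2-sided test with a 5% significance level and 90% power". It then allows for 10% dropout and arrives at 86 enrolled, the figure also given in the Abstract and under Participants. Allocation is equal, since the assistant will "randomly assign the subjects to the acupuncture group and the sham acupuncture group with ratio of 1:1". The section names neither the test nor the formula. Under Statistical analysis, the primary endpoint is analysed by analysis of covariance with baseline pain as covariate. The Wilcoxon test is mentioned there only for continuous demographic variables.

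**The concern.** The word that links inputs to result tells the reader that 76 can be recovered from the figures just given. When the calculation is run it cannot: the size and the power do not belong together on those inputs. The pair will be repeated in the results paper and checked there, and a reader who tries to reproduce it will not know whether the power, the sample size or an unstated assumption is at fault. It also misdescribes the sensitivity of the design. On the stated SDs, 38 per arm has 90% power for a difference of about 0.96 (normal) to 0.98 (Welch t) NRS points, not 1.08. What is at stake is the accuracy and reproducibility of the design statement, not the validity of the trial.

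**Working it through.** **Inputs** (all from Sample size calculation, except the 1:1 ratio from Randomization and allocation)

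- Difference in mean change: 1.74 - 0.66 = 1.08
- Sum of variances: 1.543² + 0.986² = 2.3808 + 0.9722 = 3.3530
- Equal-arm pooled SD: √(3.3530/2) = 1.295, so the standardised effect is 1.08/1.295 = 0.834
- Two-sided 5%: z = 1.960; 90% power: z = 1.282; 95% power: z = 1.645

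**Trying to reproduce the plan's 76.** The normal formula is n per arm = (z_alpha + z_beta)² × (SD₁² + SD₂²) / difference².

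- 90% power: (1.960 + 1.282)² × 3.3530/1.1664 = 10.507 × 2.8747 = 30.2, so 31 per arm and **62** in total.
- t-based check (Welch): 31 per arm gives 89.6% and 32 per arm gives 90.6%, so 32 per arm and **64** in total. The equal-variance t calculation also gives 32.

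The stated 76 is therefore not reproduced. The excess is 76 - 64 = 12 (12/64 = 19%) to 76 - 62 = 14 (14/62 = 23%).

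**Power at the stated size.** With 38 per arm the standard error is √(3.3530/38) = 0.297, and 1.08/0.297 = 3.636.

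- Normal: Φ(3.636 - 1.960) = 95.3%
- Equal-variance t: 94.8%
- Welch t: 94.7%

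**What does give 76.** The normal formula at 95% power: 12.995 × 2.8747 = 37.4, so 38 per arm and 76 in total. The match belongs to the normal formula; the t-based version at 95% gives 39 per arm (78).

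**Other readings of the inputs at 90% power (totals)**

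| Variant | Normal | t-based |
|---|---|---|
| Average of the two SDs | 58 | 60 |
| Larger SD (1.543) in both arms | 86 | 88 |
| Smaller SD (0.986) in both arms | 36 | – |
| One-sided 5% | 50 | – |
| Wilcoxon, normally distributed data | – | about 66 |

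None of these gives 76.

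**Dropout step.** 38/0.9 = 42.2, so 43 per arm and 86 in total. This agrees with the plan, so the fault lies only in the pairing of 76 with 90%.

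**The case against.** The best defence is that an unstated but legitimate allowance produced 76. The article names no test or formula, and it condenses a fuller protocol. Two routes do arrive at 76: the t-based 32 per arm divided by the minimum asymptotic efficiency of the Wilcoxon test, 32/0.864 = 37.04, rounded up to 38 per arm; and a 15% nonparametric allowance on the total, 64/0.85 = 75.3, rounded up to 76. (If the efficiency is applied before rounding, the first route gives 74.) What stands of this is that the cause is open. A reader might infer from the exact match that the calculation was run at 95% power and the power then misreported. That is plausible, but the article does not establish it. What does not stand is that the sentence is therefore correct. No allowance is stated, the Wilcoxon test is reserved for demographic variables, and the primary analysis is analysis of covariance, for which adjustment for baseline would ordinarily lower the required number.

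A second objection is that nothing is harmed, because the discrepancy is on the safe side. That is true on the stated assumptions. It limits the weight of the point without removing it.

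A reader might also infer that the Discussion contradicts the plan when it warns that "the small sample size may lead to inconclusive results". It does not. That is a general caution about a single-centre trial whose planning values come from one earlier study, not a statement about power. It is a fair one: if the SD were 1.543 in both arms, power at 38 per arm would be about 85% to 86%.

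**Conclusion.** The point holds as a reporting and reproducibility error. On the stated means, SDs, two-sided 5% level and equal allocation, 90% power needs 62 (normal) or 64 (t-based) evaluable patients, and 76 gives about 95%. The gap of 12 to 14 patients is too large for rounding or for the choice between normal and t.

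The result rests on the planning values as printed and on an unadjusted comparison of mean changes. The article gives no correlation with baseline, so no gain from covariate adjustment is credited.

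It would go too far to conclude that the trial is underpowered, that the enrolment target is wrong, or that 95% power was certainly intended. The first is contradicted by the arithmetic on the stated assumptions; the other two are not supported by the text. Nor should the 12 to 14 patients be treated as a reserve to replace patients found ineligible late: Statistical analysis commits to analysing all randomised patients by intention to treat, and the same patients cannot both supply the 95% power and stand as spares.

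**What to change.** Keep 86 enrolled and restate the size and power in one of two ways.

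- If no further allowance was used: '76 evaluable patients (38 per arm) give about 95% power for a difference of 1.08 (SDs 1.543 and 0.986, two-sided 5%); 90% power would need 64 (32 per arm).'
- If a nonparametric or variance allowance was used to reach 76 at 90% power: state that allowance, its size and the test it refers to.

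In either case, name the test or formula behind the number. The cost is one sentence, with no change to enrolment, conduct or analysis. Trial status reports that no subject had been recruited at the time of writing, so on that account the correction could precede any data.

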### Statistical analysis

The independent samples t-test or Wilcoxon rank-sum test will be used to analyze continuous variables in the demographic characteristics of the two groups, based on their normality. Categorical variables in the demographic characteristics will be analyzed using chi-squared or Fisher's exact tests. If there is a significant difference in demographic characteristics such as age, gender, and family history, they will be included as covariates in the efficacy analysis. The analysis will include all randomized BC patients based on the intention-to-treat (ITT) principle. Subgroup and sensitivity analyses may also be performed.

The change of pain intensity from baseline to 30 min after acupuncture will be analyzed by using analysis of covariance with acupuncture group and sham acupuncture treatment as factors and baseline pain intensity as a covariate. Repeated measures ANOVA will be used to assess the difference in the secondary outcomes at different time points. The degree of patients’ expectations and satisfaction with acupuncture will be evaluated using linear regression.

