#### Secondary outcome measures

The secondary end points will be evaluated as following:

i)The pain intensity will be assessed the change of NRS score from baseline to the 10 min, 20 min and 40 min after needle manipulation.ii)The degree of gastrointestinal symptoms, such as nausea, vomiting and pantothenic acid, will be evaluated for change from baseline by the visual analogue scale (VAS) at 10 min, 20 min, 30 min and 40 min after needle manipulation [32].iii)The level of anxiety during episodes of pain will be measured by changes in the VAS at 10 min, 20 min and 30 min after needle manipulation, compared to baseline [33]. The VAS will be used to assess the anxiety level of patients with BC during pain attacks.iv)The pain-related emotional responses, such as anxiety and fear, will be assessed using the Pain Anxiety Symptoms Scale-20 (PASS-20), the Fear of Pain Questionnaire-III (FPQ-III), and the Pain Catastrophizing Scale (PCS) at baseline [34–37]. The PASS-20 will be used to evaluate whether patients with biliary colic experience anxiety during the non-pain periods.v)The patients' anticipated responses to acupuncture will be evaluated using the Acupuncture Expectancy Scale (AES) at baseline [38].vi)The patient’s satisfaction for acupuncture will be monitored by the 5-point Likert scale at 30 min after needle manipulation [39].vii)The evaluation of needle sensation will be conducted using the Chinese version of the modified Massachusetts General Hospital Acupuncture Sensation Scale (C-MASS) at 10 min, 20 min and 30 min after needle manipulation [40].viii)The use of rescue analgesia will be recorded 10 min after the completion of acupuncture. The recurrence rate of BC and any adverse events occurring within 72 h after needle manipulation will be obtained through a telephone follow-up.

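### Demographic covariates enter the efficacy analysis only if a baseline significance test is positive, so the primary model is not fully fixed in advance

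*Protocol article*

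**What the plan says.** The first paragraph of Statistical analysis plans between-arm tests of baseline demographics. For continuous variables: "The independent samples t-test or Wilcoxon rank-sum test will be used to analyze continuous variables in the demographic characteristics of the two groups", the choice depending on normality. For the others: "Categorical variables in the demographic characteristics will be analyzed using chi-squared or Fisher's exact tests". The results then decide the covariates of the efficacy analysis: "If there is a significant difference in demographic characteristics such as age, gender, and family history, they will be included as covariates".

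The second paragraph gives the primary analysis of the 30-minute NRS change as "analysis of covariance with acupuncture group and sham acupuncture treatment as factors and baseline pain intensity as a covariate".

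The list of demographics is illustrative rather than closed, and no significance level is attached to the baseline tests. The section does not exempt the primary endpoint from the conditional rule, and does not say which model is primary if a baseline test is positive. It also says that subgroup and sensitivity analyses may be performed.

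**The concern.** Because allocation is random, a significant difference in age, sex or family history at baseline is a chance finding. Its p-value measures imbalance, not prognostic value, and only prognostic value makes a covariate worth having. The rule can bring in an irrelevant variable that happens to be unbalanced and leave out a prognostic one that happens to be balanced.

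It also means that the final covariate set cannot be written down before the data are seen. It depends on an open list, an unstated threshold and a triggering test that is itself chosen by a normality check. If a baseline test is positive, two primary results are available (with and without the added terms), and the article does not say which one counts.

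Three things are at stake: prespecification of the primary model, agreement between its nominal and actual error rate, and any precision that planned adjustment could have given. The Discussion concedes that the small sample may leave the result inconclusive, so the third is not idle.

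**Working it through.** **Inputs.** From Sample size calculation: mean NRS changes of −1.74 (SD 1.543) with acupuncture and −0.66 (SD 0.986) with sham; "a 2-sided test with a 5% significance level and 90% power"; 76 evaluable patients, so 38 per arm; 10% dropout; 86 enrolled. From Statistical analysis: the conditional rule, three named demographics, and baseline NRS always in the model. Assumed, because the article gives no value: a 5% level for each baseline test, independent covariates, and the share of outcome variance (R²) that the covariates explain.

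**Step 1: the article's own figures.**
- Difference: −0.66 − (−1.74) = 1.08.
- Pooled SD: √[(1.543² + 0.986²)/2] = √1.6765 = 1.295.
- Standardised effect: 1.08/1.295 = 0.83.
- Dropout: 38/0.9 = 42.2, rounded up to 43 per arm, or 86. This reproduces.
- The 76 does not follow from these inputs at 90% power, which needs 62 (normal formula) to 64 (t-test). With 38 per arm a t-test has 94.8% power. That is a separate matter, but it explains why the powers below start near 94%.

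**Step 2: how often the covariate set changes.** P(at least one positive test) = 1 − 0.95^k.
- k = 3: 1 − 0.857 = 14.3%
- k = 5: 22.6%
- k = 8: 33.7%

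The list is open, so three is the smallest natural count.

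**Step 3: type I error under the rule.** Simulation with 38 per arm, 10,000 runs, and three covariates added only when their own baseline test has p < 0.05:

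| Assumed total R² | Type I error (nominal 5%) |
|---|---|
| 0 | 4.8% |
| 0.25 | 4.3% |
| 0.49 | 3.9% |

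The Monte Carlo standard error is √(0.05 × 0.95/10,000) = 0.22 points. The first value is therefore indistinguishable from 5%, and the other two are below it. The reason is that the rule corrects the unlucky allocations, while in the remaining trials the unadjusted standard error is slightly too large. At a total R² of 0.30, for example, the mean reported standard error was 0.2297 against an actual SD of 0.2231.

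**Step 4: power at the planning effect.** Effect 0.83 SD, 38 per arm, 6,000 runs, baseline NRS in the model and taken as uncorrelated with the outcome:

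| Assumed total R² | Conditional rule | Three covariates always in |
|---|---|---|
| 0 | 94.4% | 93.6% |
| 0.05 | 94.3% | 94.3% |
| 0.10 | 94.6% | 96.0% |
| 0.25 | 94.6% | 98.0% |

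**Step 5: closed-form check on fixed adjustment.** Residual degrees of freedom fall from 76 − 3 = 73 to 70. The standard error relative to baseline NRS alone is about √[(1 − R²) × 73/70].
- R² = 0: 1.02
- R² = 0.05: 0.995
- R² = 0.10: 0.969
- R² = 0.25: 0.884

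Break-even is at R² = 1 − 70/73 = 4.1%, in line with the equal powers at R² = 0.05 in Step 4.

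**The case against.** The other side has four good arguments.

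1. The primary model is largely fixed. It always has "baseline pain intensity as a covariate", and with three tested variables about 86% of trials (0.95³) would use exactly that model. The two paragraphs can be read as a base model with possible additions. This stands: a reader might infer that the whole primary model is left to chance, or that the paragraphs flatly contradict each other, and the text supports neither. What remains is that the additions are data-dependent and that the primary model is unnamed once a test is positive.

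2. The error rate is not harmed in the direction that matters. This stands too. A reader might infer from the data-driven choice of model that false positives are inflated. Step 3 shows the opposite, and shows a departure only when the covariates are prognostic.

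3. The rule costs nothing against baseline NRS alone; any loss is relative to a different, optional model. This stands. A larger loss can be produced by assuming a smaller effect: at 0.6 SD and R² 0.25, simulated power is 73% under the rule and 82% with fixed adjustment. But 0.6 SD appears nowhere in the article, whose own figures give 0.83 SD.

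4. Nothing in the article shows that age, sex or family history predicts 30-minute pain change. This stands, so a mandatory list of added covariates cannot be derived from it.

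None of these defends the trigger itself. Nor can the point be left to an unseen analysis plan: the article states the rule affirmatively, and a plan that followed it would carry it forward.

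**Conclusion.** The point holds as a defect of prespecification. A significance test of baseline balance is the wrong criterion for choosing covariates, and as written it leaves the primary covariate set open until the data are seen: in about 14% of trials for three independent variables at an assumed 5% level, and in more if the open list grows.

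The numerical harm is small. Type I error is at or below nominal (about 4.8% down to 3.9% for assumed R² of 0 to 0.49). At the planning effect, the power forgone against fixed adjustment runs from nothing to about 3 points (98.0 − 94.6 = 3.4) for assumed R² up to 0.25. The trial's validity is not threatened. The change is still worth making, because it costs almost nothing and removes any later argument about which model was primary.

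**What to change.** In Statistical analysis:
- Remove the baseline significance tests as a trigger for adjustment, and report baseline characteristics by arm descriptively.
- State that the primary model is the 30-minute NRS change on treatment and baseline NRS, whatever the observed balance.
- If further covariates are wanted, name them now on prognostic grounds and keep them in every case. Age and sex are candidates, as is expectancy, which is already collected: "anticipated responses to acupuncture will be evaluated using the Acupuncture Expectancy Scale (AES) at baseline". Which to name, if any, is the investigators' judgement; treatment plus baseline NRS alone is sufficient.
- Report any other adjustment as a labelled sensitivity analysis, which the section already allows.

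The cost is wording, plus one degree of freedom per added covariate (73 to 70 for three). If the added covariates turn out not to be prognostic, the power loss is about 1 point (94.4% against 93.6% in Step 4). Trial status says that no subject has yet been recruited, so on the article's own account the change could precede any outcome data.

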## Methods/design

### Study design

The single center, sham-controlled, blinded, randomized trial of acupuncture treatment for BC will be executed in the First People's Hospital of Longquanyi District of Chengdu (West China Longquan Hospital Sichuan University) from May 2023 to July 2024. The protocol of trial has been approved by the Affiliated Hospital of Chengdu University of Traditional Chinese Medicine (No. 2023KL-008). And it has been registered with an identifier (ChiCTR2300070661) at ClinicalTrials.gov (https://www.chictr.org.cn/). The trial will be performed in accordance with the Standard Protocol Items: Recommendations for Interventional Trials (SPIRIT) checklist [27]. Moreover, informed consent will be obtained from all patients prior to beginning the trial. All BC patients will accept acupuncture treatment while patients are waiting for the test results after completing routine examinations. If patients with BC continue to experience pain after acupuncture treatment, conventional treatment will be administered, and the pain relief time will be recorded. The study flow chart is shown in Fig. 1, and the study time schedule is presented in Table 1.

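### Repeated measures ANOVA is fixed for the repeated secondary outcomes without a baseline covariate, and in its classical form it drops patients with any missing score; a baseline-adjusted mixed model would serve better

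*Protocol article*

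**What the plan says.** All references are to the protocol article.

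- **Method.** Statistical analysis: "Repeated measures ANOVA will be used to assess the difference in the secondary outcomes at different time points". The repeated outcomes, listed under Secondary outcome measures, are pain ("change of NRS score from baseline to the 10 min, 20 min and 40 min after needle manipulation"), gastrointestinal VAS at 10, 20, 30 and 40 min, and anxiety VAS at 10, 20 and 30 min. All three are defined as changes from baseline.
- **Baseline.** The primary analysis is an ANCOVA with "baseline pain intensity as a covariate". No such covariate is named for the repeated secondary outcomes. The only other covariate rule is conditional and concerns demographics: "If there is a significant difference in demographic characteristics such as age, gender, and family history, they will be included as covariates in the efficacy" (final word omitted). Baseline symptom scores are not demographic characteristics, so this rule does not bring them in.
- **Population.** "The analysis will include all randomized BC patients based on the intention-to-treat (ITT) principle".
- **Dropout.** Sample size calculation allows for 10%. The Discussion adds that "there is a potential for a relatively high dropout rate in the sham acupuncture group".
- **Treatment after needling.** Study design: "If patients with BC continue to experience pain after acupuncture treatment, conventional treatment will be administered". Rescue use is recorded 10 min after the 30-min session ends.

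**The concern.** Three features of the named method fit poorly with the rest of the plan.

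First, classical repeated measures ANOVA needs a score at every time point. A patient with a 10-min and a 20-min score but no 40-min score contributes nothing, not even at 10 min. The plan intends to analyse everyone randomised, and its authors think that dropout may be higher in one arm. Deletion that differs by arm can bias the comparison if those who leave differ in their symptoms from those who stay.

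Second, pain at 30 min is adjusted for baseline as a covariate, while no such adjustment is stated for the same scale at 10, 20 and 40 min. Entry requires only an NRS of at least 3, so baseline pain can range widely, and unadjusted change scores give up precision.

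Third, an overall arm effect from such a model averages over times. The 40-min pain and gastrointestinal scores may follow conventional treatment; the earlier scores should not.

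What is at stake is the secondary evidence. This includes anxiety VAS, the only listed anxiety measure taken after treatment starts, since PASS-20, FPQ-III and PCS are listed at baseline only. The article's title refers to regulating pain-related anxiety.

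**Working it through.** The plan gives no figure for the secondary analyses. Its dropout allowance does reproduce: 76 evaluable is 38 per arm, 38/0.9 = 42.2, rounded up to 43 per arm, or 86 in all. Whether 76 follows from its own inputs is a separate question that does not bear on this point.

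**1. Patients lost to complete-case fitting.** From the document: 86 enrolled, 10% dropout, at most 4 post-baseline times (gastrointestinal VAS). Assumed: the pattern of missingness, which the document does not give. If each score is missing independently with probability m, the complete fraction is (1 − m)^4:

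- m = 2%: 0.98^4 = 0.922, about 79 of 86
- m = 5%: 0.95^4 = 0.815, about 70 of 86
- m = 10%: 0.90^4 = 0.656, about 56 of 86

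**2. Precision lost relative to using all observed scores.** The quantity is the standard error (SE) of the time-averaged arm difference. Complete cases were compared with a likelihood analysis of all observed scores by simulation, with 43 per arm, 4 times, and an equal correlation of 0.5 or 0.7 between times (assumed).

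| Missingness | SE ratio, complete cases to all observed |
|---|---|
| Independent, 2% per time | 1.04 |
| Independent, 5% per time | 1.10 |
| Independent, 10% per time | 1.22 to 1.23 |
| Monotone, 10% of patients in total | 1.03 to 1.04 |
| Monotone, 20% of patients in total | 1.07 to 1.09 |

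The 10% monotone row is closest to the plan's own allowance. As a check, losing 10% of patients outright raises the SE by √(1/0.9) = 1.054 against full data. The likelihood analysis also loses some information, so the excess due to the method is smaller than 5.4%.

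**3. Precision lost by not adjusting for baseline.** Let r be the correlation between baseline and a later score (assumed) and let the variance σ² be the same at both times (assumed).

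- Change score: variance 2σ²(1 − r)
- Baseline as covariate: variance σ²(1 − r²)
- Ratio of interval widths: √[2(1 − r)/(1 − r²)] = √[2/(1 + r)]

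This gives:

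- r = 0.3: √1.538 = 1.24, about 24% wider
- r = 0.5: √1.333 = 1.15, about 15% wider
- r = 0.7: √1.176 = 1.08, about 8% wider

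**4. Timing.** If the clock runs from the start of needling, the session ends at 30 min and the 40-min scores fall 10 min later, when rescue use is recorded. Conventional treatment may have begun by then. This touches NRS and gastrointestinal VAS at 40 min. Anxiety VAS stops at 30 min and is not touched.

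**5. Bias.** No size can be given. The document says neither how many more sham patients may leave nor how their scores would differ.

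**The case against.** The best defence is that this is a preference of method for secondary outcomes measured in one session of about 40 min, described in a condensed article. A fuller protocol or analysis plan could specify imputation, a likelihood-based fit or a sphericity correction, and the article says that sensitivity analyses may be performed. At 10% monotone dropout the cost in precision is slight. Higher sham dropout is mentioned only as a possibility. A mixed model is itself biased if missingness depends on unobserved scores. All of this stands and limits the weight of the point. It does not remove it: the article positively names a method, and names it without the baseline covariate that it gives the primary outcome.

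A reader might also infer stronger points that the document does not support:

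- **That the plan contradicts its intention-to-treat statement.** It does so only if the ANOVA is fitted to complete cases without imputation, which the article does not say.
- **That ANOVA is prescribed for single-time or binary outcomes.** The sentence is limited to outcomes at different time points. For outcomes measured once, the next sentence says: "The degree of patients’ expectations and satisfaction with acupuncture will be evaluated using linear regression". No method is named for rescue use or recurrence, which an article may leave to the full plan.
- **That baseline is ignored, or that treating it as one more time level dilutes the arm effect.** The outcomes are changes from baseline, so baseline enters by subtraction. Only covariate adjustment is absent.
- **That the fall from 86 patients at 10% dropout is a price of this method.** It is the general sample-size allowance and applies equally to the primary ANCOVA.

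**Conclusion.** The point holds as a worthwhile and inexpensive improvement to the secondary analyses, not as an error that invalidates the trial.

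- **Complete cases.** The classical form of the named method is in tension with analysing all randomised patients. The loss in SE is about 3–4% if the planned 10% dropout is monotone, and reaches 22–23% only under the harsher assumption of 10% independent missingness at each of four times. Bias from unequal deletion is the more serious possibility, and it cannot be quantified from the document.
- **Baseline covariate.** Its omission widens intervals by about 24%, 15% or 8% at correlations of 0.3, 0.5 or 0.7. These figures rest on assumed correlations and equal variances. They concern precision, not validity.
- **40-min scores.** Averaging them with earlier scores would blur the pain and gastrointestinal results, because conventional treatment may have started. The anxiety result is not affected in this way.

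**What to change.** Replace the sentence on repeated measures ANOVA. For change in NRS, gastrointestinal VAS and anxiety VAS, specify a mixed model for repeated measures with arm, time, arm × time, baseline score and baseline × time, an unstructured covariance matrix, and all observed scores. Report the arm difference with its confidence interval at each time rather than one averaged effect. The endpoint definitions can stay: with baseline and baseline × time in the model, change scores and raw scores give the same arm differences.

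Report the 40-min NRS and gastrointestinal contrasts separately, stating that conventional treatment may have begun. Changing the model does not by itself deal with that, so the separate report is needed as well.

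The cost is a change of wording and slightly more programming, with no new data. The model assumes that scores are missing at random, and a sensitivity analysis should examine departures from this, including departures that differ by arm. Patients with no score after baseline still contribute nothing to the model and should be counted by arm. The Trial status section says that no subject had yet been recruited, so at that point the change could be made before any data existed.
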